## Abstract

**Background:**

Childhood antisocial behaviour has high immediate and long-term costs for society and the individual, particularly in relation to mental health and behaviours that jeopardise health. Managing challenging behaviour is a commonly reported source of stress and burn out among teachers, ultimately resulting in a substantial number leaving the profession. Interventions to improve parenting do not transfer easily to classroom-based problems and the most vulnerable parents may not be easily able to access them. Honing teachers’ skills in proactive behaviour management and the promotion of socio-emotional regulation, therefore, has the potential to improve both child and teacher mental health and well-being and the advantage that it might potentially benefit all the children subsequently taught by any teacher that accesses the training.

**Methods/Design:**

Cluster randomised controlled trial (RCT) of the Incredible Years teacher classroom management (TCM) course with combined economic and process evaluations.

One teacher of children aged 4–9 years, from 80 schools in the South West Peninsula will be randomised to attend the TCM (intervention arm) or to “teach as normal” (control arm). The primary outcome measure will be the total difficulties score from the Strengths and Difficulties Questionnaire (SDQ) completed by the current class teachers prior to randomisation, and at 9, 18 and 30 months follow-up, supplemented by parent SDQs. Secondary measures include academic attainment (teacher report supplemented by direct measurement in a sub-sample), children’s enjoyment of school, and teacher reports of their professional self-efficacy, and levels of burn out and stress, supplemented by structured observations of teachers classroom management skills in a subsample. Cost data for the economic evaluation will be based on parental reports of services accessed. Cost-effectiveness, using the SDQ as the measure of effect, will be examined over the period of the RCT and over the longer term using decision analytic modelling. The process evaluation will use quantitative and qualitative approaches to assess fidelity to model, as well as explore Head teacher and teachers’ experiences of TCM and investigate school factors that influence the translation of skills learnt to practice.

**Discussion:**

This study will provide important information about whether the Teacher Classroom Management course influences child and teacher mental health and well-being in both the short and long term. It will also provide valuable insights into factors that may facilitate or impede any impact.

The trial has been registered with ISCTRN (Controlled Trials Ltd) and assigned an ISRCTN number ISRCTN84130388. (http://www.controlled-trials.com/isrctn/search.html?srch=ISRCTN84130388&sort=3&dir=desc&max=10)

## Background

### Existing research

Childhood psychopathology is common and the prevalence of antisocial behaviour in particular has increased in recent years [1,2]. Poor socio-emotional adjustment in early childhood increases the risks of psychiatric disorder, risk taking behaviour, educational failure, and involvement in crime in both childhood and adulthood [1,2]. Affected children incur substantial costs to both society and their families [3]. The impairment and societal costs of antisocial behaviour, however, are evident throughout the population distribution rather than just among those with the highest level of problems [3]. Children in poorly managed classrooms observe that disruptive behaviour commands staff attention while good behaviour is rarely acknowledged, which may contribute to later disruptive behaviour and / or disaffection and disengagement from secondary school with the attendant risks to health and educational attainment. Teachers often complain of lack of training to manage disruptive behaviour, which is associated with higher stress levels and burn out [4-6]. An intervention that supports teachers to manage disruptive behaviour and promote socio-emotional competence could potentially benefit every child subsequently taught by that teacher as well as the teacher themselves, and could therefore be substantially more cost-effective than direct intervention with subsequent cohorts of children.

Despite a multitude of programmes targeting children [7], a recent systematic review identified that only two interventions focusing on enhancing teachers’ skills that had been studied more than once; [8] one of these was the Incredible Years (IY) Teacher Classroom Management (TCM) course. TCM was also the programme with the most robust evidence, despite the fact that there have been only two trials of TCM in isolation from other interventions [9,10]. In a small observational study in Wales, 23 teachers reported high levels of satisfaction with the TCM course. Direct observation revealed that teachers who had accessed TCM gave clearer instructions, allowed more time for compliance and their pupils were more compliant [9]. A subsequent RCT involved 12 classes (16 teachers) from 11 primary schools and 107 children aged 4–5 years [9]. The results indicated weak evidence that TCM produced changes in teachers’ behaviour and their pupil’s behaviour [9]. A second trial in Limerick involved 11 schools, 22 teachers and 207 children aged 4–7 years and detected changes in teacher’s behaviour on both observation and self-report (. There was little evidence of change in teacher-rated child well-being [10]. They estimated the intervention to cost approximately €2000 per teacher or €100 per child in schools with a class size of 20. Neither trial has been published in peer reviewed journals. Follow-up into a second year in Wales has been completed but results are not yet available, while follow-up in the Irish study is ongoing. Both studies suggest that TCM is potentially sufficiently intense to change teachers’ behaviour. Other studies involving TCM have either added additional coaching for teachers or children, and/or studied the parallel parent and child programmes with or without TCM. All suggest that TCM is potentially effective but given the additional interventions, it is impossible to estimate the impact of TCM alone as a public health intervention [11-14]. We are unaware of any other planned or ongoing trials of TCM in isolation from other interventions.

### The intervention: the teacher classroom management programme

The intervention being evaluated is the IY Teacher Classroom Management (TCM) programme [14]. TCM draws on cognitive social learning theory, particularly Patterson’s theories [15] about how coercive cycles of interaction between adults and children reinforce unwanted behaviour patterns, Bandura’s ideas [16] about the importance of modelling and self-efficacy, and Piaget’s developmental interactive learning methods [17]. In addition, it also incorporates strategies for challenging angry, negative, and depressive internal dialogue in adults whilst interacting with children, drawn from cognitive behavioural approaches. TCM is delivered to groups of ten teachers, and involves six whole-day sessions spread over a period of six months. It is delivered in a collaborative style with group leaders encouraging all to share their experience and expertise and to value that of others. The explicit goals are to: a) enhance teacher classroom management skills and to improve teacher-student relationships; b) assist teachers to develop effective group and individual behaviour plans to enable proactive rather than reactive classroom management; c) encourage teachers to adopt and promote social and emotional regulation skills; and d) encourage teachers to strengthen positive teacher-parent relationships with all parents.

TCM uses goal setting, reflective learning, video modelling, role play, rehearsal of novel management strategies, group discussion, support and problem solving, and cognitive and emotional self-regulation training. Teachers are encouraged to experiment with novel strategies between sessions and to discuss their resulting experiences. The intervention will be delivered by suitably trained and supervised ‘*group leaders’*. We envisage the same process of delivery should the trial support the implementation of TCM. The Incredible Years (IY) Foundation is collaborating to ensure that our group leaders deliver the intervention to the highest possible level and with fidelity to model. The comparator is teaching as usual (TAU). Plymouth, Torbay and Devon Local Authorities have a range of behavioural support and educational psychology services, and teachers in both arms will be able to access whatever other resources are available to them. Precisely what is accessed and how TCM might complement or supplement what is already available will be a major focus of the qualitative aspect of the process evaluation.

## Need for the current study

This study is necessary despite previous evaluations of the IY programmes, as it will be only the third evaluation of TCM in isolation from other interventions, and will be the only one sufficiently powered to detect an effect on children’s well-being. In addition, we are extending the upper age limit of children studied from seven to nine years, widening the outcome measures to include academic attainment and child and parent ratings of child well-being, focusing on the potential for particularly high impact on children living in deprived circumstances and conducting an evaluation of cost-effectiveness, none of which were a feature of earlier studies. TCM has the potential to make a major impact on the current and future mental health and well-being of the school-age population of England and to lead to substantial public sector cost savings in both the short and longer term. This study will also examine the influence of deprivation at both the school and individual level by the use of individual family and school post code to link to the Index of Multiple Deprivation and individual and school level data on free school meals. Young boys from socio-economically disadvantaged areas and / or families are particularly vulnerable to developing impairing levels of anti-social behaviour and it is important to study the impact of any intervention on this high risk group.

## Methods/Design

### Aims/objectives

· To evaluate whether TCM improves socio-emotional well-being among children as measured by the teacher completed Strengths and Difficulties Questionnaire (SDQ) cross-validated with direct observation, parental SDQ and child report on How I Feel About My School where available.

· To evaluate whether TCM improves academic attainment as measured by teacher assessment of pupil progress (APP) cross-validated with standardised assessments and SATS where available.

· To evaluate whether any improvements in well-being and attainment are sustained over the next two academic years.

· To evaluate whether TCM reduces ‘burn out’ and improves self-efficacy and well-being among teachers using the Maslach Burn Out Inventory, the Teacher Self-Efficacy Questionnaire and the Everyday Feelings Questionnaire.

· To evaluate whether TCM improves teacher’s classroom management skills using the behavioural management strategies reported by teachers in the Teacher Satisfaction Questionnaire.

· To use qualitative methods to investigate how teachers apply the strategies suggested by TCM in the classroom and any factors that may influence this process, including: year group taught, school climate and additional support and advice available to them.

· To evaluate both the utility of TCM to teachers in their practice one year after attending the course and how TCM is related to additional sources of behavioural support and school context.

· To evaluate the cost and cost-effectiveness of TCM compared to teaching as usual at final follow-up.

· To extrapolate the results from the randomised controlled trial (RCT) into young adulthood using decision analytic modelling and published data to explore the longer-term cost and cost-effectiveness implications of TCM compared to teaching as usual and to model potential cost savings in the longer term.

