#### *Embedded teacher cohort*

Control teachers will have accessed the course by T2 and T3. As control teachers access the TCM course in the second year of participation, data relating to the teachers (self efficacy, burn out and mental health and well-being) will contribute to the trial outcomes at T1 only when there is a control group. We plan to combine data from teachers in the trial with the same data collected already from the four TCM groups that we have run as part of our Feasibility Studies. Consequently, we will be able to create an uncontrolled cohort of approximately 120 teachers (eight trial groups plus four Feasibility Study groups, each of 10 teachers) to provide additional data using their baseline and national norms for comparison. It is planned that teacher self-report outcomes will be recorded once a year for up to ten years using web-based data collection. This additional study will be the subject of an alternative funding bid.

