#### *Teacher completed measures on themselves*

##### Teachers’ sense of efficacy scale [22]

A 12 item measure assesses the teacher’s perception of their sense of effectiveness as a teacher on three subscales (each with 4 items): *Student Engagement,**Instructional Practice* and *Classroom Management*. Response is on a nine point scale for each item with anchors at 1 = nothing, 3 = very little, 5 = some influence, 7 = quite a bit and 9 = a great deal. Mean scores with a range of 4–36 are calculated for each scale with a higher score indicating a greater sense of efficacy.

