##### Teacher-pupil observation tool (T-POT [26])

Teacher-child interactions will be directly observed in a sub-sample of 20 classrooms (25% of teachers) using the TPOT. This is a structured real-time frequency count of defined teacher behaviours and types of teacher-child interaction that will be carried out by observers blind to allocation. Inter-rater reliability with two or three observers rating 21 primary school teachers was high (ICC = 0.78) [25]. The focus of the observation is the class teacher.

The T-POT uses continuous coding to look for nine different teacher behaviours and seven different behaviours from the children in the class. It measures behaviours that the TCM intervention specifically targets for change and therefore will be able to assess whether the teachers’ and children’s behaviour changes between T0 and T1. ‘*Teacher negatives*’ include: physical behaviours such as restraining/moving the child; verbal behaviours such as reprimanding the child; and not being explicit to a child about the behaviour that is expected. TCM aims to provide teachers with strategies to enable them to use more positive approaches and therefore reduce the need for these negative behaviours/verbalisations. This therefore will be measurable pre- and post-intervention at T0 and T1. The T-POT also looks at ‘ *teacher positives*’, which include praise, positive physical contact, positive facial expressions and verbalisations (e.g. laughing).

All teachers have their own unique style and therefore there are no ‘cut-off’ points to indicate good or bad practice, instead the T-POT encourages comparing change between two observations, particularly in relation to ratios of positive to negative behaviours. Scores on the T-POT will be compared to the relevant items on the classroom management and instructional practice subscales of the Teacher sense of efficacy scale, and the teachers report of the TCM strategies adopted at the end of the course for those in the intervention arm.

T-POT can also assesses a range of ‘*child positives’* and *‘child negatives’* to assess whether there is any potential impact of TCM on child behaviour in the classroom, but in STARS, due to time and financial restraints, the focus of observations is on the teacher behaviour.

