#### *Quantitative data*

Data will be routinely collected relating to the administration of the TCM course. Group leaders complete standard checklists after each session that indicate which parts of the expected curriculum were covered. Standardised session evaluations and self-monitoring checklists are completed by teachers after each session to assist group leaders in planning, with a satisfaction questionnaire after the final session that collects data on the teachers’ application of the techniques covered in the course. TCM sessions will be filmed for supervision with the TCM programme developers, which allows the research team to analyse the videos for fidelity to model and contextual factors in each group. There will be eight TCM groups in total, each of 10 teachers, by the end of the trial with an additional four groups of 10 teachers from the two feasibility studies. This routinely collected data will be supplemented with data on recruitment, attendance and engagement with TCM, and with the qualitative data to provide contextual information on which to base recommendations about how TCM should be implemented successfully.

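### The secondary objective on teachers' classroom management skills names only a post-course questionnaire for attenders, so it has no concurrent control and no baseline

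*Protocol article*

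**What the plan says.** The Aims/objectives list of the protocol article includes evaluating whether TCM improves teachers' classroom management skills. The one source of evidence it names is given as "using the behavioural management strategies reported by teachers in the Teacher Satisfaction Questionnaire".

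The questionnaire appears again under Process evaluation data, Quantitative data. That section opens with "Data will be routinely collected relating to the administration of the TCM course" and describes a "satisfaction questionnaire after the final session that collects data on the teachers’ application of the techniques covered in the course". The T-POT section mentions "the teachers report of the TCM strategies adopted at the end of the course for those in the intervention arm". The questionnaire is not listed under the teacher completed measures, which are the efficacy scale, the burnout inventory and the Everyday Feelings Questionnaire.

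Control teachers teach as usual in their first year and are offered the course in their second. The Embedded teacher cohort section accordingly says that the teacher self-report data "will contribute to the trial outcomes at T1 only when there is a control group".

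Two related measures are planned at T0 and T1. The first is the efficacy scale, which has a four-item Classroom Management subscale and is described as "A 12 item measure assesses the teacher’s perception of their sense of effectiveness as a teacher on three subscales". The second is T-POT, a blinded observation of teacher behaviour in 20 classrooms. The objective names neither.

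**The concern.** The objective is worded as a causal question, but its measure is a course evaluation form. An effect of TCM on skills needs a contrast with untrained teachers or, more weakly, with the same teachers before training. The form offers neither.

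The first of the course's stated goals is to strengthen teachers' classroom management. If the child SDQ result is null, a controlled measure would help to tell whether teachers' practice failed to change or changed without benefit to pupils. The named form cannot separate these. As written, the objective cannot be answered.

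**Working it through.** **1. Which contrasts the named measure allows**

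| Contrast | Needs | What the article provides |
|---|---|---|
| Between arms at T1 | Values from control teachers in year 1 | 0 of 40: the form follows the final course session, and controls have not taken the course (Design; Quantitative data; T-POT section) |
| Before and after | A value at T0 | None: the course starts in November, after T0 and randomisation (Assessment and follow up) |
| Year-2 control attenders | An untrained comparison group | None: by then both arms have been offered the course (Embedded teacher cohort) |

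No row yields an effect estimate.

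**2. Whether another section supplies the missing measure**

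- Trial outcome measures lists child attainment and teacher stress, burn out and self-efficacy as secondary outcomes. Classroom management skill is not among them.
- Aims/objectives assigns the efficacy scale to a different objective, on burn out, self-efficacy and well-being.
- Observer completed measures says these instruments, T-POT included, are neither primary nor secondary outcomes. The abstract presents observed classroom management skills as a supplement to the secondary measures, and the T-POT section says the tool can show whether behaviour changes from T0 to T1. These statements do not agree.

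**3. The article's own power figure**

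Inputs from Proposed sample size: 40 schools per arm, 19 children each, ICC 0.15, effect 0.3 SD, 5% level (taken as two-sided).

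- VIF = 1 + (19 − 1) × 0.15 = 3.7
- Effective n per arm = 760 / 3.7 = 205.4
- Power = 86.0% by the normal approximation, or 85.1% with a t reference on 78 degrees of freedom; stated 85%
- With 34 schools per arm: 34 × 19 / 3.7 = 174.6, power 80.0%; stated 80% (Retention)

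The figures reproduce and do not depend on this objective.

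**4. Precision of the measures taken in both arms**

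The article gives no figure for these. I used a two-sided 5% t-test with one value per teacher, complete data and no baseline adjustment. The noncentrality is d × √(n₁n₂/(n₁+n₂)), with n₁+n₂−2 degrees of freedom.

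- Subscale, 40 v 40: √(1600/80) = 4.47, 78 df
- T-POT, 20 classrooms assumed to split 10:10: √(100/20) = 2.24, 18 df

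| Assumed true difference | Subscale, 40 v 40 | T-POT, 10 v 10 |
|---|---|---|
| 0.3 SD | 26% | 10% |
| 0.5 SD | 60% | 19% |
| 0.8 SD | 94% | 40% |
| 1.0 SD | 99% | 56% |
| Difference for 80% power | 0.63 SD | 1.32 SD |

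Adjusting for T0 shrinks the detectable difference by roughly √(1 − ρ²), where ρ is the T0–T1 correlation. The article gives no ρ. For an assumed ρ of 0.3 to 0.7 the factor is 0.954 to 0.714. That gives about 0.61 to 0.45 SD for the subscale and 1.26 to 0.95 SD for T-POT.

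**The case against.** The strongest reply is that this is one loosely worded bullet. Classroom management skill is not a listed outcome, the questionnaire already sits in the process evaluation, and the trial collects blinded observations and an efficacy subscale at T0 and T1. All of that stands. It lowers the weight of the point, but the objective still names a measure that cannot answer it.

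A reader might infer that the trial has no controlled information on classroom management. It does have some; the objective does not use it. A reader might also infer that post-course uptake will be reported as improvement. Nothing in the article commits to that: it restricts teacher self-report outcomes to T1 because a control group exists then, and it labels the strategies report as belonging to the intervention arm.

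The replacement measures have real limits. The subscale records perceived efficacy, from teachers who know their allocation, and already serves another objective. T-POT covers 20 classrooms, with some schools unable or unwilling to take part. The article plays down that selection because it compares data sources on the same children, an argument that does not carry over to a comparison between arms. Because baseline observation precedes randomisation, refusals at that stage would mainly limit generalisability, while losses before T1 could unbalance the arms.

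Finally, the objective and the process section use slightly different names for the questionnaire. Treating them as the same instrument is an inference, though no other satisfaction questionnaire is described.

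**Conclusion.** The point holds for this objective alone. With its named measure, the objective has no concurrent control and no baseline and cannot estimate an effect of TCM on skills. This part rests on reading the sections together and needs no numerical assumption beyond the identity of the questionnaire.

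It is moderate in weight and not a must-fix. A reader might take it as a threat to the trial's main conclusion, but the aim is secondary and at teacher level, and the primary outcome, its sample size and its 85% power are untouched.

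The detectable differences of about 0.63 SD and 1.3 SD assume complete data, no baseline adjustment and, for T-POT, a 10:10 split that the article does not state.

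**What to change.** - In Aims/objectives, tie the objective to a comparison between arms at T1, adjusted for T0, of the Classroom Management subscale in all teachers. Label it as self-perceived efficacy reported by unblinded teachers.
- Add T-POT teacher behaviours in the 20-classroom subsample as exploratory, blinded support, also adjusted for T0.
- Reconcile Observer completed measures with the abstract and the T-POT section on whether T-POT only validates other measures or also informs an effect.
- State the expected precision of both measures, so that a null result is not read as evidence of no change.
- In Aims/objectives, describe the satisfaction questionnaire as the process section already does: process data on uptake among attenders.
- If no controlled measure is adopted, reword the objective as a description of uptake and drop the question of improvement.

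The cost is an amendment to the wording of the objective and of the role of the observations. Both measures are already planned at T0 and T1, so no new data collection is needed.
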